### Economic evaluation

We are adopting a health system perspective, meaning that costs to enable rolling out the GHI are traced as incurred by the GHS / MoH and its development partner, the GIZ, but excludes costs incurred by the health facilities or patients. Economic costs are estimated but not restricted to financial costs, i.e., the full value of resources being used by any of the parties (MoH; GHS; and GIZ) involved in implementation of the intervention is traced, whether reported in financial statements or not. We rely on Activity Based Costing, i.e., an approach that recognizes the relationship between costs, activities, and products. Accordingly, all activities are mapped and related to the design and pilot implementation of the GHI; then, all resources being consumed by these activities are traced; and finally, all resources being consumed are valued [43].

To collect data on resource consumption and unit costs, we use a mix of financial statements from implementing partners and key informant interviews. The main activities regarding GHI implementation will comprise of: Design, Management, Promotion, Operations research, Monitoring and Evaluation (M&E), Verification, and Supply Side activities. We will ask the implementation team to generate aggregate cost information across specific micro-level activities, which will then be grouped into broader meaningful Cost Categories, and Analysis Cost Categories, to enable drawing a link between Cost Categories and Main Activities [43].

A descriptive cost analysis and budget impact analysis is carried out to inform the nation-wide scale-up of GHI. This may be supplemented with a modelled analysis where the effects and costs are modelled beyond the outcome observed during the study period. This will allow comparative assessment of the value for money that GHI offers compared to usual care. It will also allow comparison with other government initiatives as to their cost-effectiveness in terms of cost per disability-adjusted life year (DALY) averted.

The budget impact analysis is used to identify costs and resources required for offering/expanding the GHI to all patients seeking care at the health facilities in Ghana. The budget impact analysis tracks the total and per participant costs of programme delivery using an activity-based costing (ABC) approach [44]. Using this approach, all relevant labor, materials and supplies, contracted services, travel vouchers and opportunity costs required to deliver the interventions are captured by key activities.

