The Ghana Heart Initiative (GHI) initiated in September 2018, and offi cially launched on 9th January 2019, introduced an innovative health system intervention to strengthen early detection, and management of hypertension and CVD across health facilities in the Greater Accra Region (GAR). The initiative was implemented as a collaborative effort by the Deutsche Gesellschaft für Internationale Zusammenarbeit (GIZ) GmbH, Ministry of Health (MoH) and the Ghana Health Services (GHS). The GHI (“the intervention”) enables frontline healthcare workers to better address the needs of patients and communities and support advocacy and policy that promotes effective care for CVD. The intervention does not target the single patient but changes the quality of care given to the single patient, by changing the way the health system addresses the management of risk factors (such as hypertension) and CVD. The overarching goal of this study is to conduct a rigorous evaluation of the GHI, a supply-side intervention implemented in 42 diverse health facilities (primary to tertiary care level) for the prevention and management of hypertension and CVD in the GAR, adopting a mixed-methods implementation science approach.

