## Methods

### Study Setting

Ghana is a lower-middle-income country with an average annual per-capita gross domestic product of US$2,445.3 [18]. The mortality from coronary heart disease in 2020 was 119.93 per 100.000 population, and the probability of dying from any of CVD, cancer, diabetes and chronic respiratory disease is 20.8% [19]. The health system in Ghana is decentralized, pluralistic, and operates on an integrated three-tier (national, regional, and district) scheme and incorporates a community-level health delivery system to support community-based primary healthcare [20]. Most healthcare is provided by the government and is largely administered by the service delivery agencies under the MoH such as the Ghana Health Service (GHS), teaching hospitals, and the private providers (self-financing, faith-based, and non-governmental organisations). Ghana reformed its National Health Insurance Scheme in 2003 with 40% of the population being enrolled and ~ 60% enrolled people are exempted from premium payments [21]. Ghana is one of the first African nations to enact legislation and earmark financing for universal health coverage; a significant move towards health system strengthening and improved financial protection [21].

Accra is the capital city of Ghana and is located in GAR, which is one of the 16 administrative regions, and has the highest population density. The GAR has 26 districts, including the Accra Metropolitan Assembly, and had a total population of 5.4 million in 2021. The pilot phase of the GHI was implemented in 42 health facilities located in five districts (Accra Metro, Tema Municipal, Ga East, Ga West, Dangme West and Dangme East). A health facility is an infrastructure built and licensed by the Health Facilities Regulatory Authority to take care of the healthcare needs of the citizens of Ghana.

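### The budget impact analysis counts opportunity costs on a design-and-pilot cost base, which overstates the outlay for scale-up unless separated, and its per-participant unit is undefined

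*Protocol article*

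**What the plan says.** All of this is in the protocol article; unless noted, in its Economic evaluation section.

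- **Purpose.** The budget impact analysis is to identify the costs and resources for extending GHI to patients at health facilities across Ghana. The Abstract also ties it to the nationwide scale-up.
- **Measure.** "The budget impact analysis tracks the total and per participant costs of programme delivery using an activity-based costing (ABC) approach".
- **Content.** Under this approach "all relevant labor, materials and supplies, contracted services, travel vouchers and opportunity costs required to deliver the interventions are captured by key activities".
- **Type of cost.** "Economic costs are estimated but not restricted to financial costs". Resources used by the ministry, the health service and the development partner are valued in full, including those that appear in no financial statement.
- **Base.** In the costing, "all activities are mapped and related to the design and pilot implementation of the GHI". The main activities are "Design, Management, Promotion, Operations research, Monitoring and Evaluation (M&E), Verification, and Supply Side activities".
- **Nature of the intervention.** The Background says: "The intervention does not target the single patient". The Study intervention section lists five components: stakeholder engagement and national guidelines, staff training with coaching, equipment, data-collection training with routine-data indicators, and a round-the-clock support centre.

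**The concern.** A budget impact analysis tells a payer how much money an expansion will need. An economic cost answers a different question: the value of everything used, paid for or not. The time of staff already on the payroll has a value, but using it needs no new funds. The article draws this distinction itself, then names opportunity costs as part of the budget impact analysis.

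The pilot base raises a similar issue. Designing the programme and doing operations research on it are largely one-off. Some of the products already exist nationally: the section on design strengths and weaknesses says the guidelines were signed in 2021, launched in August 2022 and can be reached through an app. Expansion need not buy these again.

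The unit is the third issue. GHI's components are acquired per facility, per staff member or once for the country. A cost per participant is not a natural unit for them, and the costing text does not say who counts as a participant.

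At stake is the figure that a ministry would read as the price of going national.

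**Working it through.** The article gives no cost, budget, participant count or scale-up total, so there is no stated figure to reproduce. The check is a comparison of the text plus an illustration with assumed shares.

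**1. Opportunity costs**

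Let *s* be the share of the economic cost that is opportunity cost (assumed). If none of it becomes an outlay at scale-up, outlay = (1 − s) × economic cost, and

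overstatement = 1/(1 − s) − 1.

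- s = 10%: 1/0.90 − 1 = 11%
- s = 20%: 1/0.80 − 1 = 25%
- s = 40%: 1/0.60 − 1 = 67%

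If a fraction *c* of it does become an outlay, the formula is 1/(1 − s(1 − c)) − 1. With s = 20% and c = 0.5 (also assumed) this is 1/0.90 − 1 = 11% instead of 25%.

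**2. One-off costs**

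Let *d* be the one-off share of the pilot's economic cost (assumed). If it is scaled up along with the rest, the ratio of the unseparated figure to the outlay is 1/(1 − d − s).

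- d = s = 10%: 1/0.80 = 1.25
- d = s = 30%: 1/0.40 = 2.50

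This step depends on design costs entering the budget impact analysis, which the text leaves open. The general costing covers design and pilot, while the budget impact paragraph speaks of programme delivery. No split of one-off from recurrent cost is stated.

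**3. Unit**

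Set side by side, the measure is total and per-participant cost, the target population is patients seeking care, and the components are facility-, staff- or national-level inputs. The section on the quantitative component uses study participants for both providers and patients, so it does not settle the meaning. No sentence says how the pilot cost becomes a national one. With no extrapolation rule, no error can be computed.

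**The case against.** Three arguments on the other side have weight.

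- **The stated aim covers resources as well as costs, which is wider than cash.** This is fair, and reporting opportunity costs is not wrong in itself. But a scale-up figure that merges them with outlays does not show what must be funded, and the article mentions no separation.
- **Design costs in the budget impact analysis are an inference.** This stands, so that part of the point is conditional. Activities are costed as distinct items, so the split can be made from the planned structure.
- **Some non-cash pilot items will have to be bought at scale-up.** This also stands. It is why the 11%, 25% and 67% are upper illustrations for their shares and why donated items should be priced in.

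A reader might go further and infer that the national figure will be the pilot cost per participant multiplied by national patient numbers. Because Greater Accra "has the highest population density", the result would then be too low for quieter facilities, and the total could err in either direction. The article does not support this. It tracks total as well as per-participant cost and states no such multiplication. Population density is not patient volume per facility. The 42 pilot facilities run from primary to tertiary care, and control facilities in two other regions were matched on outpatient volume. A condensed article may also leave the extrapolation method to the full protocol.

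**Conclusion.** The point holds in a limited form. The article explicitly places opportunity costs in a budget impact analysis, and the only cost base it describes is the full economic cost of design and pilot. Carried forward unseparated, these items can only push the scale-up figure above the required outlay. The illustrated overstatement is 11%, 25% or 67% for opportunity shares of 10%, 20% or 40%. It rests on assumed shares and on none of those costs becoming outlays. The effect of one-off costs is additional, but conditional on their being included.

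These percentages concern the named items only, within the stated perspective. That perspective leaves out costs borne by facilities and patients, so they are not an estimate of the net error of the whole figure.

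The per-participant unit is undefined and sits poorly with a facility-level programme. That calls for a definition and a stated scaling unit; neither a size nor a direction of error follows from it. It would also go too far to say that the result cannot serve as a budget, because the planned data allow the separation. Clinical outcomes are not affected.

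**What to change.** In the budget impact analysis:

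1. Report financial outlays separately from economic and opportunity costs. Value donated pilot items that scale-up must buy at purchase price. Keep the economic and opportunity costs for the analysis of cost per disability-adjusted life year averted.
2. Separate one-off costs (design, guideline and app development, operations research) from recurrent costs, and identify those already spent.
3. Build the scale-up total from recurrent cost per facility at primary, secondary and tertiary level, plus national lines such as the support centre.
4. Define participant, and present cost per participant as descriptive only.

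The cost is a modest amount of extra tabulation. Costs are already collected by activity, with financial statements as one source. National facility counts by level are also needed; the bodies that supplied facility characteristics for matching should hold them, though the article does not say so. The headline becomes less simple than one cost per participant.

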## Discussion

There has been no published scientific evaluation of a multicomponent health system intervention to strengthen hypertension and CVD prevention and control in Ghana, but reviews of studies in other high-income settings show favorable results for guideline-based care and equivocal results regarding training of healthcare workers, and providing equipment support and CVD call center support [31] [45] [46]. Moreover, these mostly small, single-strategy studies with short test periods have tended to focus on intermediate or surrogate endpoints and had limited economic evaluation and sustainability. For these reasons, we sought to comprehensively assess an integrated, and multicomponent CVD risk reduction intervention tailored in Ghana. The GHI introduces integrated care across the healthcare levels by implementing guideline-based prevention, diagnosis, and treatment of hypertension and CVD, training of physician / healthcare worker, supply of equipment for diagnosis and management of CVD, data management support for continuous monitoring and improvement and a CVD call support center operating day and night (“24/7”). Further, the GHI intends to improve the provider’s adherence to guidelines through mentoring/supervisory visits and deliver high quality care to patients with hypertension and CVD.

### Evaluation Design Strengths and Weaknesses

The mixed-methods triangulation study is the first of its kind for LMICs and in sub-Saharan Africa, testing a comprehensive and multifaceted health system intervention addressing hypertension and CVD management. The evaluation is rigorously designed, factoring in multiple data sources, minimizing biases using matched control health facilities, data triangulation using quantitative survey and qualitative interview data, and economic evaluation. The ToC was developed in a participatory manner in collaboration with GHI programme implementers helping the evaluators to understand where the intervention tried to produce a change and led to a commonly defined TOC and definition of indicators. Our focus is centered more on a theory-driven evaluation and the fact that we will work “closer to reality” but far from a real experiment or quasi-experiment. To avoid contamination between the intervention and control facilities, the data collection for control group facilities and participants will be accomplished by a separate team of trained field enumerators. However, in a real-world setting we cannot avoid spillover of intervention components to other regions since the national guidelines for the management of CVD were signed by the Minister of Health in 2021 and offi cially launched in August 2022 by the MoH and is available in the public domain and can be accessed via the AkomaCare App (https://akomacare.org/download) [47]. The data collection timepoints for the MRR before and after GHI implementation has been prespecified in both the intervention and control health facilities to avoid any seasonal variations in the hypertension and CVD care outcomes. Furthermore, we customized the survey questionnaires developed with an open-source platform called Survey Solutions (https://mysurvey.solutions/en/) developed by the World Bank. Data is entered on Android-based tablets using the Survey Solutions Interviewer App, stored locally on the tablets, and synchronized regularly to HIGH’s virtual server, enabling real time tracking and remote data monitoring. The Survey Solutions Designer allows the inclusion of instructions visible in blue for each question as the interviewer progresses through the survey. This digital data collection approach along with its technical features improves data quality and reduces data entry errors or missing values.

The study has several limitations. As health facilities are not randomly assigned to the intervention and control arms, it is possible that the arms will be imbalanced about important patient characteristics (age, disease patterns, severity), provider characteristics (education, professional training or practicing experience), facility characteristics (primary, secondary and tertiary) and ownership (public, quasi-government and faith-based). These would be addressed in analyses adjusted for any important patient or provider-level characteristics. Mixed methods (quantitative and qualitative assessments) data evaluation will complement the overall data triangulation and analytical approach. Another potential limitation of the evaluation process may be recall bias when obtaining interview data after the pilot implementation phase of the intervention, as adherence may vary.

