**Methods::**

This study adopts a mixed- and multi-methods design comparing the effects of the GHI in 42 intervention health facilities (i.e. primary, secondary and tertiary) in the Greater Accra Region versus 56 control health facilities in the Central and Western Regions. The evaluation design is guided by the RE-AIM framework underpinned by the WHO health systems building blocks framework, integrated by the Institute of Medicine’s six dimensions of health care quality: safe, effective, patient-centered, timely, effi cient, equitable. The assessment tools include: (i) a health facility survey, (ii) a healthcare provider survey assessing the knowledge, attitudes, and practices on hypertension and CVD management, (iii) a patient exit survey, (iv) an outpatient and in-patient medical record review and (v) qualitative interviews with patients and various health system stakeholders to understand the barriers and facilitators around the implementation of the GHI. In addition to primary data collection, the study also relies on secondary routine health system data, i.e., the District Health Information Management System to conduct an interrupted time series analysis using monthly counts for relevant hypertension and CVD specific indicators as outcomes. The primary outcome measures are performance of health service delivery indicators, input, process and outcome of care indicators (including screening of hypertension, newly diagnosed hypertension, prescription of guideline directed medical therapy, and satisfaction with service received and acceptability) between the intervention and control facilities. Lastly, an economic evaluation and budget impact analysis is planned to inform the nationwide scale-up of the GHI.

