### Conceptual framework

In line with the abovementioned implementation science approach and the aforementioned research questions, our study adopts the RE-AIM framework as the guiding operational evaluation framework. The RE-AIM framework offers a comprehensive structure that will guide the quantitative and qualitative data collection to systematically evaluate the robustness of the intervention (“the GHI”) across the RE-AIM domains – reach, effectiveness, adoption, implementation, and maintenance as well as related costs, and the potential for scaling up the intervention to other regions in Ghana [22]. It should be noted, that within the effectiveness domain, some of the indicators may have elements to estimate impact, where we hope to carry out a Difference-in-Difference (DID) analysis and if routine health data is available an interrupted time series-analysis (ITSA) enabling a quasi-experiment to attribute causality to the intervention.

The Theory of Change (ToC) development was informed by a discussion with stakeholders of how the intervention (“the GHI”) induced changes in the management of hypertension and CVD care in a “real-world setting”, a description of the health systems pathway through which this change was expected to happen, and the RE-AIM evaluation framework to assess whether and how change has happened [23] [24].

Considering the content of our intervention specifically, we turned to the World Health Organization’s (WHO) six health system building blocks (HSBB) to structure our work [25]. We did so out of a desire to analyze systematically how the actions carried out by the GHI had produced effects on each of the six HSBB. The WHO HSBB at health facilities enables a comprehensive evaluation of the health system performance, clinical, processes of care and quality of care outcomes. Further, understanding implementation outcomes (fidelity, acceptability, and effectiveness) of the intervention using a conceptual ToC model from diverse user’s perspectives can support consideration of how and why the intervention is likely to generate the changes observed and assist in thinking through the potential for the expansion and scale-up of the GHI in contextually similar settings. It may also contribute to consideration of how to manage implementation over time and highlight factors that are likely to support the sustainability and achievement of long-term goals of the GHI.

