
### Data collection Tools, Indicators, and Strategies

The quantitative evaluation component is critical to learning whether intervention improves outcomes among patients seeking care for hypertension and CVD in health care facilities. This component includes the following sets of quantitative tools, specifically:

**Facility based structured survey**, including analysis of facility registries & clinical records, to capture indicators of quality-of-service delivery (input, process, outcome).**Interviews with healthcare providers** to assess the knowledge, attitude, and practice regarding hypertension and CVD.**Exit interviews with the patient** to assess the client’s perception of the CVD consultation or examination, as well as his / her recollection of the instructions that he / she received about treatment or preventative behaviour.**Review of medical records** to capture indicators of quality-of-service delivery before and after GHI implementation.**Health management information systems** data with data being aggregated monthly at facility level for each of the CVD outcomes of interest.

The rationale for selecting service delivery, processes of care, clinical and quality of care indicators are based on the aspirations to achieving optimal health service performance and to guide the health care planning as a continuous quality improvement tool to drive health service improvement and better health outcomes [30] [31]. The outcome indicators are chosen from the recommendations of the national and international guidelines focused on CVD as well as to reflect how the facility or provider level determinants affect individual health behaviour and wellbeing (Table 1).

The exit survey draws questions from previous patient exit and household surveys and were further adapted to fit the Ghanaian context. Demographic and socioeconomic questions were based on the Ghana Census and Demographic and Health Survey. The exit interviews with the patient examines the respondent’s perception of the CVD consultation or examination, as well as his/her recollection of the instructions that he/she received about treatment or self-care behavior. The survey also captures how patients perceive the quality of specific aspects of the health facility and its providers. Patients are asked to rate 27 aspects of the facility visit on a five-point Likert scale with related Emoji’s.

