The medical records of outpatient and inpatient folders at two cross-sectional timepoints before and after GHI implementation are being reviewed to assess between group differences in hypertension and CVD care delivery. Eligibility of medical records are pre-specified based on confirmed diagnosis of hypertension or CVD, and complete medical records with at least data available on patient demographics (age, sex), medical history (confirmed case of hypertension or CVD), laboratory results (any test prescribed, or test reports reviewed), and medical treatment or prescription.

Lastly, DHIMS2 data routinely collected by the MoH in Ghana to monitor service provision consisting of monthly facility-specific counts for a wide range of services, including CVD will be analyzed to assess the differences in care delivery between the intervention and control health facilities over the time period. In line with prior work, to translate monthly counts into indicators that adequately capture service coverage, we construct outcome variables that account for the underlying target population living in the catchment area of a given facility [32]. More specifically, we apply interrupted time series analysis to DHIMS2 data to assess impact on the following CVD indicators: prevalence of hypertension, coronary heart disease, stroke, heart failure and related mortality.

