### Study outcomes

The primary outcome measures being assessed between the intervention and control facilities are: i) proportion of screened individuals for hypertension, ii) newly diagnosed patients with hypertension or CVD, iii) prescription of guideline directed medical therapy for hypertension and CVD, iv) BP control defined as < 140/90 mmHg, v) provider knowledge and practice related to hypertension and CVD and vi) patient centered care and satisfaction. The study also assesses several secondary outcome measures including difference in total waiting time for physician consultation and physician acceptability of the GHI.

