### Statistical analysis

Quantitative data is analyzed by descriptive statistics for demographic, socio-economic and other patient-, provider- and health system level factors between the intervention and control facilities. Differences in service delivery indicators, process of care measures (prescription of guideline directed medical therapy) and clinical outcomes (BP control) will be compared between the intervention and control facilities. The chi-square test is used to evaluate differences between categorical variables. Two-sided p-values < 0.05 will be considered statistically significant. Composite performance scores are defined by determining the proportion of patients who receive concordant care compared to patients who receive discordant care between the intervention and control facilities. Linear and logistic regression analysis techniques are used to assess determinants of health outcomes, processes of care measures, and treatment satisfaction [33]. Random-effects regression analyses will be used to account for cluster effects and imbalances between intervention and control group health facilities; Effect sizes will be presented as risk ratios for binary outcomes, and as mean differences for continuous outcomes; 95% confidence intervals (CI) will be given for both. Missing data in outcome measures will be handled by appropriate imputation methods.

A propensity score will also be created using logistic regression and will contain those variables associated with treatment at a health facility [34]. Analysis of clinical outcomes analysis will also use ANCOVA (analysis of covariance) to compare the prescription of evidence-based medicines, and mean change in BP and lipids between the intervention and control arm facilities [29]. Other outcome measures such as behavioural and biochemical risk factors will be analyzed using logistic or conditional logistic regression to adjust the comparisons for other variables. We shall also compare the percentages achieving clinical and behavioural targets between the intervention and control arm facilities.

The fidelity analysis will uncover the extent to which the GHI was fully or partially implemented by various health system stakeholders.

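### One enumerator team per arm: in the exit survey, the provider survey and any undifferenced record comparison, a team difference cannot be told from a GHI effect

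*Protocol article*

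**What the plan says.** The Discussion section on design strengths and weaknesses gives the purpose, "To avoid contamination between the intervention and control facilities", and then the measure: "the data collection for control group facilities and participants will be accomplished by a separate team of trained field enumerators". The arms also lie in different regions: "42 intervention health facilities (i.e. primary, secondary and tertiary) in the Greater Accra Region versus 56 control health facilities in the Central and Western Regions".

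Two of the six primary outcomes listed under Study outcomes come from interviews: "v) provider knowledge and practice related to hypertension and CVD and vi) patient centered care and satisfaction". The exit survey is a set of subjective ratings: "Patients are asked to rate 27 aspects of the facility visit on a five-point Likert scale". The record review has two periods: "The medical records of outpatient and inpatient folders at two cross-sectional timepoints before and after GHI implementation are being reviewed".

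The Statistical analysis section plans direct between-arm contrasts, for example that "clinical outcomes (BP control) will be compared between the intervention and control facilities", using chi-square tests, random-effects regression, a propensity score and ANCOVA. Difference-in-difference appears only under Conceptual framework, for some effectiveness indicators, "where we hope to carry out a Difference-in-Difference (DID) analysis". The limitations paragraph promises adjustment for patient and provider characteristics. It does not mention differences between the data collection teams.

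**The concern.** Enumerators can differ in how they prompt on rating items, put knowledge questions, judge whether a folder is complete enough to be eligible, and read blood pressures and prescriptions from a record. When each team works in one arm only, any average difference of this kind enters the arm contrast as if it were an effect of the GHI. A larger sample does not shrink it.

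The two surveys have no earlier round to difference against. Under Quantitative study component, before-and-after measurement is attached to the record review alone. The programme's first phase ran from 2018 to 2020, while the evaluation was designed from April 2022. Enumerators in GHI facilities can also recognise the arm, because acceptability of the GHI is asked only there.

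The stated reason does not clearly offset this. Enumerators deliver none of the five GHI components, and the article describes no route by which they would contaminate control facilities. The spillover it does describe runs through the published national guidelines and the app, which separate teams do not block.

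**Working it through.** The article gives no figure for differences between teams, so there is nothing to reproduce. Three checks were made.

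**1. Can arm be separated from team after the intervention?** Take one row per facility, 42 intervention and 56 control, with columns for intercept, arm and team. Because team = 1 − arm, the correlation of arm and team is −1 and the 98 × 3 matrix has rank 2. The arm effect is not estimable once team is in the model. Random facility effects, a propensity score or ANCOVA covariates do not change this, since none of them adds variation in team within an arm.

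**2. Does a before-after record comparison help?** Stack two periods (196 rows) with columns for intercept, arm, team, time and arm × time. The rank is 4 for 5 columns, but the arm × time term is estimable. A team difference that is constant over time and additive on the analysis scale therefore cancels, provided the same team abstracts both periods in its arm.

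**3. How large could the consequence be?** Illustration for a binary outcome.
- Inputs from the article: 1,200 participants in total, 20% non-response or missing data, two-sided α = 0.05, 10% relative difference.
- Assumed: equal split, control rate 50%, no clustering, no true GHI effect, team difference b.
- Evaluable per arm: 1,200 × 0.8 / 2 = 480.
- Planned effect at this rate: 0.10 × 50% = 5 points.
- SE = √(2 × 0.25 / 480) = 0.0323.
- False-positive rate ≈ Φ(b/SE − 1.96) + Φ(−b/SE − 1.96).

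| Team difference b | b/SE | False-positive rate |
|---|---|---|
| 0 | 0 | 5% |
| 2 points | 0.62 | 10% |
| 3 points | 0.93 | 15% |
| 5 points | 1.55 | 34% |

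Around a rate of 60% the last three become 10%, 16% and 36%. With an assumed design effect of 2, SE = 0.0323 × √2 = 0.0456, and the rates for 3 and 5 points fall to about 10% and 20%. The bias is still b in every case.

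**4. What would crossing the teams achieve?** Suppose each team covers a share of the facilities in the other arm. The variance inflation of the arm effect is 1/(1 − r²), where r is the correlation of arm and team. It is infinite now. It would be about 2.7 with 10% of facilities crossed (r = −0.794), 1.6 with 20% (r = −0.609), 1.2 with 30% (r = −0.384) and 1.0 with 50% (r = 0). These shares are illustrative.

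**The case against.** The article describes real safeguards: trained enumerators, one tablet questionnaire with on-screen instructions, real-time tracking with remote monitoring, record eligibility fixed in advance, and knowledge items scored by a set rule. Fuller training or agreement checks may sit in field manuals that an article leaves out. This stands in part. Such measures may make team differences small, but they cannot measure or remove what remains while team and arm coincide.

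A reader might infer that all control-arm data are compromised. The documents do not support that. DHIMS2 counts are routine data that no enumerator generates, and the record review spans both periods, so on the natural reading each team abstracts both in its own arm. The point does not extend to those sources when the records are analysed by difference-in-difference.

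A reader might also infer that enumerators cannot possibly contaminate controls. That is too strong. Staff who have handled GHI material in intervention facilities could conceivably carry some of it to control respondents. What can be said is that the article describes no such route.

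The size is open to challenge as well. The control rate, equal split, absence of clustering and team differences are all assumed, and the calculation is for a proportion, whereas the ratings and part of the knowledge analysis are scores. The article does plan random-effects models for clustering. All of this stands, and the percentages should be read as an illustration.

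**Conclusion.** The point holds for the exit survey, the provider survey and any record comparison not differenced over time. There team is completely aliased with arm, and this follows from the stated assignment without any numerical assumption. The limitations paragraph does not acknowledge it. The likely size is unknown. At an assumed 50% rate, a 5-point team difference would equal the whole planned effect, and smaller differences would raise the false-positive rate by the amounts shown.

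It should be corrected, but it does not invalidate the evaluation. DHIMS2 analyses are untouched and the record review has a ready remedy. For the record review the conclusion depends on whether difference-in-difference is actually used, which the article only hopes for, and on each team abstracting both periods in the same way.

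**What to change.** - For remaining field work, train the existing enumerators together and assign them so that each works in both intervention and control facilities. Even a partial crossover makes the arm effect estimable. Record enumerator ID and include it in the models.
- Make difference-in-difference the main record comparison, with the same team abstracting both periods wherever teams are not crossed.
- Where abstraction is complete, have each team re-abstract a small random set of the other arm's folders, and report between-team agreement beside the results. This helps the record review only.
- Where exit or provider interviews are complete, list the aliasing of team and arm as a limitation on the satisfaction and knowledge contrasts.
- Either describe the contamination route that separate teams are meant to block, or drop that justification.

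The cost is some travel between regions and a small re-abstraction exercise. Crossing the teams does not remove regional confounding, because region stays aliased with arm, and it does not blind enumerators to arm.
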